## Abstract

**Introduction:**

Neonatal death and later disability remain common sequelae of hypoxic-ischaemic encephalopathy (HIE) despite the now standard use of therapeutic hypothermia (HT). New therapeutic approaches to brain protection are required. Melatonin is an indolamine hormone with free-radical scavenging, antiapoptotic, anti-inflammatory and gene regulatory neuroprotective properties, which has extensive preclinical evidence of safety and efficacy. Pharmacokinetic (PK) data suggest it is necessary to reach melatonin levels of 15–30 mg/L within 6–8 hours of hypoxia-ischaemia for brain protection. We developed a novel Good Manufacturing Practice (GMP) grade melatonin in ethanol 50 mg/mL solution for intravenous use. In preclinical studies, ethanol is an adjuvant excipient with additional neuroprotective benefit; optimised dosing protocols can achieve therapeutic melatonin levels while limiting blood alcohol concentrations (BACs).

**Methods and analysis:**

The Acute High Dose Melatonin for Encephalopathy of the Newborn (ACUMEN) Study is a first-in-human, international, multicentre, phase 1 safety study of intravenous melatonin in babies with moderate/severe HIE receiving HT. Sixty babies will be studied over two phases: a dose escalation study including four dose levels to establish the recommended phase 2 dose (RP2D), followed by a 6-month cohort expansion study of RP2D to further characterise PKs and affirm safety. Participants will receive a 2-hour intravenous infusion of melatonin within 6 hours of birth, followed by five maintenance doses every 12 hours to cover the period of HT. Plasma melatonin and BACs will be monitored. The RP2D will be based on the attainment of therapeutic melatonin levels while limiting BACs and the frequency of dose-limiting events (DLEs). A Bayesian Escalation with Overdose Control approach will be used to estimate the risk of DLE per dose level, with a target level of <33%. ACUMEN will establish a network of centres with standardised neurocritical care and harmonised MRI systems for the analysis of the primary outcome—magnetic resonance spectroscopy (MRS) lactate to N-acetylaspartate peak area ratio localised to the basal ganglia and thalamus and include a nested blood biomarker study to explore early disease severity indicators.

**Ethics and dissemination:**

Approval has been given by the London Central National Health Service Health Research Authority Ethics Committee (25/LO/0170) and UK Clinical Trials Authorisation from the Medicines and Healthcare products Regulatory Agency. Separate approvals have been sought in Ireland and Australia. Dissemination will be via peer-reviewed journals, conference presentations, public registries and plain language summaries for parent/legal guardian(s), in accordance with national requirements.

**Trial registration number:**

ISRCTN61218504. EU CT: 2025-520538-49-00.

**Protocol version:**

Publication based on the UK protocol V.3.0, 08 May 2025

STRENGTHS AND LIMITATIONS OF THIS STUDYThe Acute High Dose Melatonin for Encephalopathy of the Newborn (ACUMEN) Trial is a phase 1 safety and dose escalation study which will establish the recommended phase 2 dose of a novel melatonin formulation in the target high-risk population of babies with moderate/severe hypoxic-ischaemic encephalopathy (HIE) who are being treated with therapeutic hypothermia, a treatment which is only partially effective.Dose escalation decisions will be contingent on safety and established target melatonin levels, based on robust safety, efficacy and pharmacokinetic preclinical data.The ACUMEN Trial uses a Bayesian Escalation with Overdose Control approach to estimate risk of dose-limiting events with accumulating trial safety data to support dose escalation decisions.A network of 10 large, tertiary neonatal units across the UK, Ireland and Australia, with experience of recruiting into neonatal and HIE trials and a standardised level of neurocritical care, will establish a network for future phase 2 trials.The requirement for the loading dose to be administered within 6 hours is necessary but challenging in this multicentre study.

## Introduction

### Background and clinical need

 Hypoxic-ischaemic encephalopathy (HIE) is a leading cause of neonatal mortality and morbidity, affecting 2–3 babies per 1000 live births in high-income countries.^1^ Therapeutic hypothermia (HT) is currently the only treatment available for moderate/severe HIE, and, while partially effective, babies still develop an unacceptable level of long-term neurological sequelae. Almost two decades since the initial cooling trials and adoption as standard care for moderate/severe HIE in 2010 in the UK, there has been limited progress to further improve outcomes. Recent data highlight that, despite HT, more than 50% of babies die or develop neurodevelopmental impairment, including 10%–19% with cerebral palsy.^2 3^ Long-term neurological sequelae remain of concern despite treatment optimisation;^3^ up to 60% of children develop neurocognitive, behavioural or executive processing problems, impacting learning.^4^ Importantly, follow-up of the original cooling trial cohorts shows that persistent neurological impairment later in childhood, impacting IQ, non-verbal performance score, processing speed, working memory and behaviour, is common.^5 6^

Further attempts to optimise cooling protocols with longer and deeper cooling did not improve outcomes^3^ and new therapies are urgently needed. Promising therapies such as inhaled Xenon^7^ and Erythropoietin^2^ have not demonstrated treatment benefit in phase 2 and 3 trials, respectively, despite indications of potential benefit in large animal preclinical studies.^8^,^10^ A phase 3 randomised controlled trial to assess intravenous allopurinol with HT has been stopped early after recruiting 503 babies due to early indicators of lack of benefit of the intervention (EudraCT 2016-000222-19).

The Acute High Dose Melatonin for Encephalopathy of the Newborn (ACUMEN) Study is a first-in-human, international, multicentre phase 1 safety trial of melatonin to augment HT brain protection for moderate/severe HIE.

### Melatonin

Melatonin (N-acetyl-5-methoxytryptamine) is a promising therapy to translate from bench to cot side, with a pleiotropic profile for neuroprotection supported by comprehensive preclinical safety and efficacy data. The neuroprotective actions of melatonin include potent free radical scavenging properties, anti-inflammatory and antiapoptotic activities and gene regulatory effects on melatonin receptors (MT1 and MT2).^11^ These benefits inhibit the initiation of the injurious neurotoxic cascade leading to cell death during the period of secondary energy failure (from ∼6 hours after birth), thereby reducing adverse neurological outcomes.

While enteral forms of melatonin are readily available, the development of an intravenous formulation remains a key challenge. Melatonin has limited solubility in aqueous solution and the need to develop highly concentrated formulations acceptable for intravenous use in neonates necessitates the use of excipients, of which several have been used, in preclinical studies (including cyclodextrin, dimethyl sulfoxide and polysorbate). However, ethanol has shown the most favourable safety profile given its adjuvant, partial neuroprotective effects observed in animal models of HIE (in addition to HT)^12 13^ and adult stroke.^14^,^17^

The investigational medicinal product (IMP) is a novel melatonin in ethanol (50 mg/mL) manufactured in accordance with Good Manufacturing Practice (GMP) under a manufacturing authorisation licence for intravenous administration. The IMP will require dilution in 5% glucose to a final melatonin concentration of 2.5 mg/mL for intravenous infusion. The dosing regimen for this study has been optimised to maintain therapeutic melatonin levels while limiting the accumulation of ethanol and its by-product, acetaldehyde, as discussed below.

### Preclinical data

A preclinical systematic review and meta-analysis of 14 animal studies of hypoxia-ischaemia (HI) at term-equivalent age^18^ was an important milestone towards clinical translation to babies with HIE, along similar lines as the evolving guidelines for clinical translation in adult stroke included in the Stroke Therapy Academic Industry Roundtable (STAIR) criteria.^19^

In summary, we observed: (1) A significant reduction in brain infarct size (pooled standardised mean difference (SMD) −2.05, 95% CI −2.93 to −1.16, p<0.001, n=110 animals assessed), (2) Improved neurobehavioural outcomes (SMD −0.86, 95% CI −1.23 to −0.53, p<0.001), (3) Reduction in cell death (SMD −0.60, 95% CI −1.06 to −0.14, p=0.006). The overall observed effect size in all three outcomes combined remained significant (SMD −0.92, 95% CI −1.26 to −0.58, p<0.001). Importantly, subgroup analysis demonstrated benefit of melatonin as an adjunct to cooling with SMD −0.89, 95% CI −1.63 to −0.16, p<0.001, compared with HT alone, giving confidence in the added benefit of melatonin to HT. The meta-analysis also demonstrated that studies using formulations containing ethanol were most effective (SMD −1.14, 95% CI −1.64 to −0.65, p<0.001). This is supported by the intermediate improvement in neurological outcomes in newborn piglets administered ~300 mg/kg ethanol following HI.^12^

Intravenous melatonin has demonstrated consistent evidence of brain protection in newborn piglets^812 20^,^22^ and fetal lamb^23 24^ models of HIE. The key studies in newborn piglets are summarised in online supplemental table S1. These large animal studies are translationally relevant; the newborn piglet has a similar gyrencephalic brain structure and brain development comparable to newborn babies.^25^ In addition, neurocritical care monitoring (continuous video amplitude-integrated electroencephalography (aEEG/EEG)) and magnetic resonance spectroscopy (MRS)) are used as robust biomarkers in the piglet studies, giving translational relevance. In term neonates with HIE, evolution of the aEEG background pattern and time to recovery conveys prognostic information.^26^ Recovery of aEEG/EEG to either continuous or discontinuous normal voltage is associated with better prognosis, with the maximum predictive time at 48–72 hours.^27^ The clinical importance and relevance of lactate to N-acetyl aspartate peak area ratio (Lac/NAA) is based on clinical studies of babies with HIE in whom basal ganglia and thalamus (BGT) proton (^1^H) MRS accurately predicts 2-year motor, cognitive and language neurodevelopmental outcomes.^28 29^

Over the last 15 years the University College London (UCL) Neonatal Neuroprotection Research Group has focused on preclinical studies assessing safety, pharmacokinetics (PKs) and neuroprotective efficacy of intravenous melatonin in the newborn piglet; together, these studies give the foundation for the optimised dosing regimen in the clinical phase 1 ACUMEN Trial.^812 20^,^22^ These data suggest that the attainment of therapeutic melatonin levels of 15–30 mg/L within 6–8 hours of HI is necessary for optimal brain protection. Critically, a loading dose of 20 mg/kg is required to rapidly achieve therapeutic levels after birth, while 12-hourly maintenance doses of 10 mg/kg every 12 hours from 24 hours ensure therapeutic levels are maintained over time (see figure 1). This dosing regimen minimised blood ethanol (alcohol) concentrations (BACs), particularly during maintenance dosing (see figure 1B); we observed no evidence of accumulation of the alcohol by-product, acetaldehyde.^22^ These preclinical studies support the safety, PKs and efficacy of intravenous melatonin for clinical use in neonates.

**Figure 1 F1:**
[figure not shown]
Melatonin and ethanol levels in 13 newborn piglets. Piglets received a loading of 20 mg/kg of melatonin over 2 hours (arrow) followed by four maintenance doses of 10 mg/kg over 2 hours every 12 hours from 24 hours. Target melatonin level (15–30 mg/L) (**A**) and BAC <0.25 g/L shaded (**B**).

No significant physiological safety concerns were observed with intravenous melatonin dissolved in ethanol. In study 1 (Table S1), there was no difference in mean arterial blood pressure during the 6-hour melatonin infusion and no difference overall in inotrope use.^20^ Most recently in study 5, there was no difference in mean arterial blood pressure, although we observed a clinically non-significant, mild increase in inotropic support following the loading dose (increase in vaso-inotropic score equivalent to a dopamine dose of 5 mcg/kg/hour).^22^ We observed no toxic effects of intravenous melatonin on haematology (full blood counts) and blood biochemical monitoring (liver function and renal function).

### Newborn lamb studies

The Monash Group demonstrated robust neuroprotection using a similar melatonin formulation containing ethanol at similar doses of 15–17 mg/kg^23 24^ but with a dosing regimen similar to a continuous infusion. Following umbilical cord occlusion, newborn lambs were administered melatonin 60 mg, dissolved in ethanol, given as 5 mg bolus intravenous injections every 2 hours from 30 mins after birth until 24.5 hours of life. Melatonin-treated animals showed a significant reduction in Lac/NAA, improvement in achieving neurobehavioural milestones and reduction in immunohistochemical markers of cerebral brain injury. There was no report of hypotension or need for increased inotropic support, although increased drowsiness was observed. Treatment benefit was additive to cooling, supporting the data from the newborn piglet studies.^24^ While this dosing regimen also shows promise, a 2-hour infusion used in the piglet studies may be more suitable in critically unwell infants.

### Clinical data

This is a first-in-human phase 1 clinical trial using a melatonin in ethanol formulation for intravenous use in HIE. To date, one other pilot study of intravenous melatonin administration has been conducted in this target population of term babies using a non-ethanol containing melatonin formulation.^30^ There are also limited pilot data of enteral administration of melatonin in this target population. These studies were underpowered with limited PK data reported, using high enteral doses up to 80 mg (~27 mg/kg).^31^

Jerez-Calero *et al* conducted the only clinical study of intravenous melatonin administration in babies with HIE receiving cooling.^30^ The melatonin formulation contained melatonin 6.5 mg/mL dissolved in propylene glycol and macrogol. Twelve babies with moderate/severe HIE undergoing HT received a daily dose of 5 mg/kg melatonin administered within 6 hours of birth intravenously over 2 hours every 24 hours for 3 days. Compared with HT+placebo (0.9% sodium chloride), melatonin-treated infants demonstrated similar laboratory haematology, renal, liver, metabolic and coagulation parameters. Melatonin was not associated with increased seizure activity and MRI findings did not differ significantly between groups. At 18 months, melatonin-treated infants achieved higher cognitive scores and a trend to improved language scores. Melatonin was associated with reduced systemic proinflammatory cytokines.^32^ The authors concluded that melatonin was considered safe. The benefit on neurological outcomes remains inconclusive given the confounding effects (higher Sarnat Score in the placebo group) and small sample size of the study. Detailed PK data and adverse events (AEs) data were not reported.

Clinical studies of melatonin in babies with HIE meeting eligibility criteria for HT are now needed to assess safety and PKs. Based on reassuring safety data for intravenous melatonin dosing at 5 mg/kg, we plan for dose escalation starting at an intravenous loading dose of 5 mg/kg over 2 hours with five maintenance doses of 2.5 mg/kg over 2 hours every 12 hours from 24 hours. AEs and melatonin, BACs and, in *sentinel* babies, acetaldehyde levels will be measured to provide a comprehensive assessment of the recommended phase 2 dose (RP2D).

### Justification for the melatonin dosing regimen

The IMP will be administered intravenously as a loading dose within 6 hours of birth (T0) followed by five (half-dose) maintenance infusions from 24 hours (T0+24 hours) every 12 hours to cover the period of cooling and rewarming. All infusions will be given over 2 hours with close safety monitoring. Multiple doses of melatonin over this period are necessary given the evolving brain injury over hours and days after HI.

Given the lack of PK data in babies, dose escalation will proceed over four dose levels to achieve the target melatonin levels of 15–30 mg/L (based on the preclinical data), while assessing safety, and ensuring the BACs remain <0.25 g/L. Dose escalation will start at a dose of 5 mg/kg (plus five maintenance doses of 2.5 mg/kg), which has already been shown to be safe in this target population in a different formulation.^30^ Incremental increases of 5 mg/kg with subsequent dose levels are based on reassuring PK data for melatonin and BACs from simulations of a population PK model in newborn piglets. Each dose level chosen will be based on predictions from the concurrent human PK data as the ACUMEN Study progresses. Doses up to 30 mg/kg may be given based on the No Observed Adverse Events Level (NOAEL) in piglets.

While no absolute limit in BACs in medicines is stipulated by the UK Medicines and Healthcare products Regulatory Agency (MHRA) given the sparse safety evidence, we have set a limit of 0.25 g/L to align with previous recommendations.^33^ This balances the partial benefit of ethanol for HIE while limiting potential toxicity (BAC >1 g/L in rodents).^34^ In newborn piglets, this threshold does not lead to significant accumulation of acetaldehyde,^22^ the by-product of ethanol metabolism implicated in the systemic effect of ethanol toxicity. Blood acetaldehyde concentration will be measured in *sentinel* babies to ensure levels do not exceed 2.2 mg/L where mild, transient effects of facial flushing and tachycardia may present without other significant adverse effects.^35^,^38^

## Methods and analysis

### Study objectives

The overall aim of the ACUMEN Study is to assess the safety of four intravenous dose levels of melatonin in babies with moderate/severe HIE receiving HT.

The primary objectives are:

Safety profile assessment: to assess the safety profile of melatonin across all dose levels being studied based on the occurrence of a dose-limiting event (DLE).The attainment of putative therapeutic plasma melatonin levels (15–30 mg/L) across dose levels being studied.The attainment of putative BACs safety (<0.25 g/L) across dose levels being studied.To identify the RP2D.

The secondary objectives are:

PK model: To establish the PK profile of intravenous melatonin infusion in term infants with HIE undergoing HT.Feasibility of the neonatal neuroprotection trial network: To assess the feasibility of developing a neonatal neuroprotection trial network for future phase 2 RCTs.Recruitment feasibility: To assess the feasibility of recruiting participants within 6 hours of birth.

The exploratory objectives are:

Biomarker discovery feasibility: To assess the feasibility of developing a standardised approach to exploratory blood biomarker discovery integrated with neuroprotection trials to identify early markers of HIE severity and treatment response.Dose-response assessment: To evaluate the dose-response curve for intravenous melatonin infusion in the target population.To develop a physiologically based PK model of melatonin and ethanol.

### Trial design

This multicentre, phase 1 safety study will recruit from level 3 neonatal intensive care units (NICUs) with experience in managing babies receiving HT for HIE across England, Scotland, Ireland and Australia. We aim to recruit 60 babies with moderate/severe HIE receiving HT starting August 2025, in two phases: (1) A 12-month dose escalation phase, to establish safety and identify the RP2D (24–39 babies), and (2) A 6-month cohort expansion phase, to affirm safety and PK of the RP2D (21–36 babies).

### Dose escalation procedure

The dose escalation phase (illustrated in figure 2) will assess up to four dose levels using the six potential doses listed in table 1. Participants will be allocated to a single dose level and overall, a minimum of three participants will be enrolled per dose level. AEs, based on the Neonatal Adverse Event Severity Score (NAESS)^39^ and blood samples over six time points, will be collected to measure melatonin and BACs as shown in figure 2.

**Figure 2 F2:**
[figure not shown]
Melatonin dosing regimen and timing of pharmacokinetic (PK) blood sampling (**A**) and illustration of the principles of the dose escalation study design (**B**). Four dose levels will be assessed with a *sentinel* baby (red circle) at each dose level to ensure levels of melatonin (<33.5 mg/L), ethanol (<0.25 g/L) and acetaldehyde (<2.2 mg/L) are within safety thresholds after the loading dose. Subsequently, a further two babies at each dose level will be recruited prior to review of safety and PK data by the DSMB. Recommendations by the DSMB to the Trial Steering Committee to either (1) Dose escalate (2) Continue the same dose level for a further cohort of three babies, or (3) Reduce the dose (from dose level 2). The DSMB will also be called for review if there are any dose-limiting events. The figure is an illustration of one possible path of dose escalation in ACUMEN. Other paths, including with dose de-escalation or repeats of dose levels, are possible. Created in BioRender. [name] (2025) https://BioRender.com/xlkdsdd. MRS, magnetic resonance spectroscopy.

**Table 1 T1:** Melatonin doses under investigation based on the NOAEL of 30 mg/kg observed in piglets

Dose level	Loading dose at T0	5 maintenance doses (from T0+24 hours)
Dose 1	5 mg/kg	2.5 mg/kg
Dose 2	10 mg/kg	5 mg/kg
Dose 3	15 mg/kg	7.5 mg/kg
Dose 4	20 mg/kg	10 mg/kg
Dose 5	25 mg/kg	12.5 mg/kg
Dose 6	30 mg/kg	15 mg/kg

NOAEL, No Observed Adverse Events Level.

Dose level 1 will start with a loading dose of 5 mg/kg given within 6 hours of birth (T0) followed by five maintenance doses of 2.5 mg/kg from T0+24 hours every 12 hours. Blood melatonin levels and BACs will be measured over six time points based on PK modelling using piglet data.

The first baby recruited to each dose level will be a *sentinel* baby and subjected to the following safety precautions:

They must have *moderate *HIE based on aEEG/EEG or Modified Sarnat Neurological Examination.In addition to plasma melatonin and BAC, acetaldehyde levels will be measured following the loading dose (at T0+2 hours) and data made available prior to subsequent maintenance dose to ensure the following PK safety limits are met:Plasma melatonin <33.5 mg/LPlasma acetaldehyde <2.2 mg/LBlood alcohol concentration <0.25 g/L.If melatonin, BACs and acetaldehyde levels are not within the stated levels or not available, no further doses will be administered. In addition, further IMP administration to the *sentinel* baby must *not *continue if the *sentinel* baby experiences a DLE.

The clinical summary, safety and PK data will be reviewed by the Data Safety and Monitoring Board (DSMB) following 100 hours after last IMP administration (‘DLE safety window’) to determine whether the recruitment to the dose level may continue. Once safety has been confirmed in the *sentinel* baby, recruitment of subsequent babies may occur in parallel. Due to logistical constraints, only melatonin levels and BACs will be measured for the remaining participants at this dose level.

The DSMB will review the safety and PK data following the recruitment of the third baby in a cohort. The DSMB will recommend to the Trial Steering Committee (TSC) one of the following possible outcomes: (1) Recruit at the next dose level, (2) Continue recruitment at the current dose level, (3) Reduce dose to one of the previous dose levels (where relevant), or (4) Stop the trial. Dose escalation decisions will be based on both the concurrent accumulating safety (suspected DLEs) and PK data, and their predictions at the next dose level. For PK, the trial pharmacologist will develop a population-PK model to simulate the plasma melatonin levels and BACs at the next dose level. If PK modelling predicts that melatonin systemic exposure will be equal to or exceed the Cmax of 33.5 mg/L and Area under the serum concentration vs. time curve for 0-24h (AUC24) of 454.7 mg*h/L or the BAC safety threshold (<0.25 g/L), that dose level will not be opened to recruitment. For DLE predictions, a Bayesian Escalation with Overdose Control (EWOC) approach will be used. EWOC uses a statistical model to estimate the risk of DLE per dose level with the target level of DLEs set at 33% for this trial. While awaiting dose escalation decisions (from the second dose level onwards), and in the absence of DLEs in the first three babies, a maximum of three further babies can be recruited to the current dose level after approval from the DSMB. In the event of a DLE, or having recruited the three additional babies, backfilling^40^ to the previous dose level can occur while awaiting the dose escalation decision. Data acquired from additional babies will be included in a subsequent dose escalation report for review by the DSMB/TSC. Backfilling will be limited to a maximum of 15 babies in the dose escalation study.

The subsequent dose escalation will proceed to dose level 2 at a loading dose of 10 mg/kg and maintenance doses of 5 mg/kg. Subsequent doses for dose level 3 and dose level 4 will be determined by the safety and PK model prediction. Provided that dose levels 1 and 2 have not exceeded the maximum BAC safety threshold and no other dose-limiting toxicity is encountered, further escalation will be recommended. Using the parameters of a population PK model, dose escalation will be evaluated. The possible scenarios are:

The model predicts the dose to achieve the melatonin target is lower than the dose to reach the dose-limiting BAC threshold. In this case, dose level 3 will aim to achieve the melatonin target.The model predicts the dose to achieve the melatonin target is equal to the dose to reach the dose-limiting ethanol target. In this case, dose level 3 will be set at one level below the predicted target dose.The model predicts the dose to achieve the melatonin target is greater than the dose to reach the dose-limiting ethanol target. In this case, dose level 3 will be set at the level predicted to be immediately below the predicted dose-limiting ethanol cut-off.

Following dose level 3, the PK model will be updated and dose level 4 set according to a dose level predicted to be immediately below the predicted dose-limiting BAC cut-off. At the end of the dose escalation phase, RP2D will be established.

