### Criteria for discontinuing or modifying interventions

Any discontinuation or modification of doses will be in line with the trial design and in accordance with the dose escalation procedure confirmed by the DSMB and TSC. Reasons for discontinuing treatment include:

Serious Adverse Event (SAE) or “severe” AE, that is, grade 3 and above on the Neonatal Adverse Event Serverity Scale (NAESS)^39^ considered related to IMP (definition of suspected DLE)PK exposure cap of melatonin (<33.5mg/L), ethanol (<0.25g/L) or acetaldehyde (<2.2mg/L) exceeded (this will be available concomitantly in the *sentinel* baby only). PK exposure cap of melatonin, ethanol or acetaldehyde predicted to exceed at the subsequent dose escalation.Withdrawal of consent by parent/legal guardian(s).A decision made by the treating clinician based on any change in the infant’s condition that justifies the discontinuation of treatment.

The analysis will be by intention to treat. Participants who discontinue protocol treatment, for any of the above reasons, should remain in the trial for the purpose of follow-up and data analysis. A blood sample will be collected at the time of termination and an additional sample 24 hours after the last IMP administration. These samples will be analysed for PK purposes to characterise the plasma levels of melatonin and ethanol.

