### Interim review of DLEs and dose escalation decisions

Interim review of the safety and PK data will be performed as follows: (1) After each *sentinel* baby (2) After recruitment of a cohort of three infants per dose level for dose escalation decisions and (3) After a suspected DLE. The purpose of the interim review will be to affirm safety and PK. Following completion of the DLE safety window (100 hours after last IMP administration), the safety and PK data will be source-verified by the sponsor and presented to the DSMB for review. The DSMB will review the data and advise the TSC on whether dosing at the current level may continue (for example after a *sentinel* baby or DLE event) or whether a dose escalation to the next dose level is recommended (after a cohort of three babies at a dose level). For the *sentinel* baby at each dose level, no other baby may be recruited until the interim safety and PK data have been reviewed by the DSMB/TSC. For the purpose of dose escalation decisions, the trial statistician and pharmacologist will provide updated estimates of dose-limiting toxicity and PK predictions at the next dose level. In the cohort expansion phase, the safety and PK data will be reviewed after every 10 babies. No interim analysis will be performed for the secondary and exploratory outcomes.

The study will be terminated if any of the following stopping rules are satisfied:

Emergence of new therapies for HIE of greater benefit to this population.The DSMB recommends terminating the trial for safety reasons or if any evidence suggests that the risk-benefit ratio of the clinical trial is unfavourable.AEs: The incidence or severity of AEs in this study indicates a potential risk to patients taking part in the trial. Any isolated NAESS grade 5 AE (death) considered related to the IMP will result in immediate stopping of recruitment at the current dose level. No further participants will be recruited to that dose level until review by the DSMB and TSC.PK: If the observed or predicted melatonin, ethanol, or acetaldehyde levels exceed their respective Cmax cap in the *sentinel* baby, further dosing at this dose level must not proceed until DSMB/TSC review.Significant protocol deviation, lack of compliance or cooperation on the part of an investigator, which endangers the safety of the participants or the validity of the trial.

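### The rule that keeps a dose level closed joins the melatonin Cmax and AUC24 limits with *and*, conflicts with other clauses that use the Cmax cap alone, and does not say over which part of the regimen Cmax is predicted

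*Protocol article*

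**What the plan says.** All places are in the protocol article.

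- **Dose escalation procedure** (rule for opening a level). The trigger for melatonin is a prediction described as "equal to or exceed the Cmax of 33.5 mg/L and Area under the serum concentration vs. time curve for 0-24h (AUC24) of 454.7 mg*h/L". The sentence goes on "or the BAC safety threshold (<0.25 g/L), that dose level will not be opened to recruitment". So *and* stands between the two melatonin limits and *or* before BAC.
- **Criteria for discontinuing or modifying interventions.** One reason is "PK exposure cap of melatonin (<33.5mg/L), ethanol (<0.25g/L) or acetaldehyde (<2.2mg/L) exceeded", noted as available concomitantly for the sentinel baby only. A further reason looks ahead: "PK exposure cap of melatonin, ethanol or acetaldehyde predicted to exceed at the subsequent dose escalation". The melatonin cap is a single concentration, and any one analyte suffices.
- **Interim review of DLEs and dose escalation decisions.** The PK stopping rule begins "If the observed or predicted melatonin, ethanol, or acetaldehyde levels exceed their respective Cmax cap in the" sentinel baby. Its consequence is a halt to further dosing at that level until the DSMB and TSC have reviewed.
- **Figure 2 legend and sentinel precautions.** The sentinel check is that "levels of melatonin (<33.5 mg/L), ethanol (<0.25 g/L) and acetaldehyde (<2.2 mg/L) are within safety thresholds after the loading dose".
- **Setting of dose level 4** (end of Dose escalation procedure). It has "dose level 4 set according to a dose level predicted to be immediately below the predicted dose-limiting BAC cut-off", and names neither melatonin limit.

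AUC24 appears in the first of these rules and in no other.

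**The concern.** The rule for opening a level is a fixed exposure gate in a first-in-human neonatal trial. It decides which doses are studied and so which can become the RP2D. Its logic should be readable in only one way.

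There are two difficulties. First, the conjunction: taken at its word, melatonin closes a level only when both limits are reached, whereas BAC closes it alone. The clauses elsewhere that also speak of predicted levels act on the Cmax cap alone. The same prediction can therefore be barred by one clause and not by another. Second, the window: AUC24 is defined over 0 to 24 hours, which ends when the first maintenance dose is due, but no window is given for Cmax. A dose level consists of a loading dose and five maintenance doses, so the predicted Cmax could be the post-loading peak or a later, accumulated one. The choice can change which of the two limits is reached first.

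**Working it through.** **Logic check.** Suppose predicted BAC is acceptable.

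| Predicted breach | Opening rule, read literally | Predicted-cap clause under Criteria for discontinuing | If either limit alone closed a level |
|---|---|---|---|
| Cmax only | does not bar | acts | bars |
| AUC24 only | does not bar | silent | bars |
| Both | bars | acts | bars |

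The first row is a conflict between passages. The second is a gap: only the opening rule mentions AUC24, and read literally it does not act.

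**Can one limit be breached without the other?** The article gives no derivation of 33.5 or 454.7, so neither can be reproduced. The illustration below uses:

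- from the article: 2-hour infusions (Justification for the melatonin dosing regimen); maintenance doses at half the loading dose (Table 1), at T0+24, 36, 48, 60 and 72 hours (Participant timeline);
- inferred: a half-life of 100/5 = 20 h, because AEs reporting equates 100 hours with five half-lives;
- assumed: a linear one-compartment model, with k = ln 2 / half-life.

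*Step 1, loading dose only.* With C2 the level at the end of the loading infusion,

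AUC24/C2 = [2 − (1 − e^(−2k))/k] / (1 − e^(−2k)) + (1 − e^(−22k))/k.

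At 20 h, k = 0.03466 and the ratio is 1.01 + 15.39 = 16.40 h. The ratio of the two limits is 454.7/33.5 = 13.57 h. The two ratios agree only at a half-life of about 12.2 h, so the limits are not interchangeable.

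*Step 2, Cmax taken as the loading peak, 20 h.* AUC24 reaches its limit at C2 = 454.7/16.40 = 27.7 mg/L. At C2 = 33.5 mg/L, AUC24 is 33.5 × 16.40, about 550 mg*h/L, which is 21% over its limit. AUC24 binds first. The 27.7 mg/L lies inside the 15–30 mg/L target range.

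*Step 3, Cmax taken over all six infusions, 20 h.* The peak falls at T0+74 h. Relative to C2 it is

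0.5 × (1 + e^(−12k) + e^(−24k) + e^(−36k) + e^(−48k)) + e^(−72k) = 0.5 × 2.572 + 0.082 = 1.37.

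The regimen peak reaches 33.5 mg/L when C2 = 33.5/1.368 = 24.5 mg/L, and AUC24 is then 24.5 × 16.40, about 402 mg*h/L. Cmax binds first. Under the literal *and*, the level would not be barred by melatonin until AUC24 also reached 454.7, at a regimen peak of 27.7 × 1.368 = 37.9 mg/L.

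*Step 4, other half-lives.*

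| Half-life | C2 when AUC24 = 454.7 | AUC24 when loading peak = 33.5 | AUC24 when regimen peak = 33.5 |
|---|---|---|---|
| 10 h | 36.9 | 412 | 412 |
| 15 h | 30.7 | 497 | 437 |
| 20 h | 27.7 | 550 | 402 |
| 30 h | 24.9 | 612 | 352 |

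At 10 h the loading peak is also the regimen peak, so the last two columns agree and Cmax binds first on either window. At 15 h and longer the order depends on the window.

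**The case against.** The strongest reply is that the opening rule does not stand alone. It says when a level stays closed, not that every other level opens. The DSMB and TSC review safety and PK data at each escalation, and the predicted-cap clause, if applied, already catches a Cmax-only breach. This is right. A reader might infer from the *and* that a level predicted to exceed the Cmax cap would open unchecked. The article does not support that: for Cmax the defect is conflicting clauses, not a missing safeguard.

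It is also fair that concentration-only limits are natural where the rule acts on measured sentinel levels, since one sample at T0+2 h cannot give an AUC24. Only the clauses about predicted levels are proper comparators, and of these the Interim review clause is a sentinel pause, not a rule for opening a level.

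On the remaining AUC24-only gap, the reply is that it nearly disappears if Cmax is taken over the whole regimen. Across half-lives of 4 to 60 h in this model, AUC24 at a regimen peak of 33.5 mg/L never exceeds about 456, or 0.3% over its limit. That stands too, but it depends on a window the article does not give.

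Finally, *and* may have been meant to list two separate limits, and UK protocol V3.0, which the article condenses, may be explicit. Possibly so. But the article states the rule itself, and the *or* before BAC in the same sentence favours the joint reading.

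**Conclusion.** The point holds as an inconsistency in a stated decision rule. Read literally, the opening rule does not bar a level predicted to breach only one melatonin limit. That conflicts with the predicted-exceedance clauses for Cmax, and for AUC24 no other passage acts. The window for Cmax is unstated, and in the 20-hour illustration it reverses which limit binds: AUC24 at a loading peak of about 27.7 mg/L, or Cmax with AUC24 at about 402 mg*h/L.

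The textual conflict needs no model. The figures rest on an assumed linear one-compartment model, an inferred half-life and a chosen Cmax window. A reader might take the 21% at 20 h as the largest possible disagreement, or equate it with the step between two doses in Table 1. Neither follows. On the same loading-peak basis a 30-hour half-life gives 612/454.7, about 35% over. The article has no human PK model that would show whether any Table 1 dose falls in the disputed range.

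**What to change.** Reconcile the opening rule under Dose escalation procedure with the predicted-exceedance clauses under Criteria for discontinuing or modifying interventions and under Interim review of DLEs and dose escalation decisions. Use one explicit logical statement, repeated identically in the PK report to the DSMB. It should say:

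1. whether any single limit or only a combination keeps a level closed;
2. whether AUC24 is part of the rule, and in which of these passages;
3. over which part of the regimen Cmax and AUC are predicted (loading dose only, or all six infusions).

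Which rule is right is for the sponsor to decide. The cost is a wording change in three passages and in the PK report template, with no change to data collection or sample size.
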